# Impact of exercise training on cardiotoxicity and cardiac health outcomes in women with breast cancer anthracycline chemotherapy: a study protocol for a randomized controlled trial

**DOI:** 10.1186/s13063-019-3499-9

**Published:** 2019-07-15

**Keywords:** Breast cancer, Cardiotoxicity, Cardiac healthcare, Supervised exercise, Supportive cancer care

## Abstract

**Background:**

Anthracyclines are chemotherapeutic agents frequently used in breast cancer (BC) treatment. Although it improves disease-free and overall survival, the use of anthracyclines is associated with a cumulative risk of cardiac toxicity. Preventive strategies to optimize cardiac health are needed and exercise is proposed as a potential non-pharmacological approach for counteracting anthracycline-related cardiotoxicity (ARC). Most of the data on the effects of exercise to reduce ACT are from animal studies, with only a few studies in a limited number of patients indicating beneficial effects. To better understand the effectiveness of exercise in the mitigation of ARC, clinical, real-world trials claim require a larger sample size and more accurate and valuable clinical biomarkers. In this study, we intend to include a large sample and investigate cardiac function through serial measures of biomarkers and imaging techniques.

**Methods:**

This protocol describes a two-arm, prospective, randomized controlled trial that will explore the cardioprotective effect of a structured exercise program in women with BC undergoing anthracycline-containing chemotherapy (ACT). Ninety adult women with early BC and recommended to receive ACT will be randomly assigned (1:1) to an intervention group or a control group. Patients allocated to the intervention group will perform a supervised exercise program three times per week, consisting of a combination of aerobic and resistance training with progressive intensity and volume, during the time period they receive ACT. The control group will receive standard BC care. Primary outcomes related to cardiac (dys)function will be circulating N-terminal pro-brain natriuretic peptide (NT-proBNP) levels, resting left ventricular (LV) longitudinal strain, and resting LV ejection fraction. Secondary outcomes will include the assessment of resting blood pressure, resting heart rate (HR), resting HR variability (HRV), recovery HR, physical function outcomes, self-reported physical activity level, health-related quality of life, and fatigue. Data will be obtained at baseline (t_0_), after the end of anthracycline-treatment (t_2_), and 3 months after t2 (t_3_). Additionally, NT-proBNP will be measured 1–24 h prior to each anthracycline-treatment cycle (t1).

**Discussion:**

The implementation of the present study design, using novel clinical biomarkers, will determine the effect of structured exercise interventions at mitigating ARC, with the overall aim of finding means to further improve BC care.

**Trial registration:**

ISRCTN, ISRCTN32617901. Registered on 24 October 2018. Last updated on 11 January 2019.

**Electronic supplementary material:**

The online version of this article (10.1186/s13063-019-3499-9) contains supplementary material, which is available to authorized users.

## Background

Over the last three decades the epidemiology of breast cancer (BC) has been marked by the clear increase in survival rates [1]. The accessibility of screening and the discovery of new therapeutic options are among some relevant factors related to the improved management of cancer. However, despite their undeniable clinical importance, anti-cancer treatments are also associated with frequent induction of side effects. Among those, cardiotoxicity emerges as a major challenge, limiting treatment options [2] and contributing to morbidity and mortality in this patient population [3–5].

In the BC setting, cardiotoxicity is typically associated with exposure to traditional cytotoxic therapies and particularly with the use of anthracyclines [6]. Anthracyclines are important and effective chemotherapeutic agents, frequently administered in curative and palliative regimens for BC, although their clinical use is limited by cardiac dysfunction, usually seen as cardiotoxicity [7]. The American Society of Echocardiography and European Association of Cardiovascular Imaging define cardiotoxicity as a decrease in left ventricular ejection fraction (LVEF) of > 10% to a value of < 53% [8]. However, it has been proposed that anthracycline-related cardiotoxicity (ARC) is a continuous [9] and dose-dependent phenomenon [10] that starts with acute myocardial damage [11], which can be detected by elevation of circulating cardiac biomarkers [12] and by impairment of left ventricular (LV) longitudinal strain [13], in turn preceding the commonly reported progressive decline in LVEF [9]. ARC may ultimately lead to overt heart failure, particularly when underestimated, not prevented or insufficiently prevented, or untreated, [9].

Unfortunately, and in addition to the manifestations associated with anthracycline treatment, BC survivors often exhibit a phenotype characterized by the presence of risk factors for cardiovascular disease (CVD), including advanced age, obesity, prior CVD, poor cardiorespiratory fitness, and inappropriate lifestyle (smoking, alcoholism, and sedentary lifestyle) [14, 15]. It is therefore not surprising that when compared to healthy individuals of a similar age, these patients have higher prevalence of CVD and greater mortality [4]. Considering the high risk of cardiac dysfunction, the study of preventive strategies is an emerging and unmet need, as these strategies may mitigate cardiac damage associated with the use of cardiotoxic agents and could lead to improvements in overall cardiovascular health.

In adults with CVD without cancer, exercise training is recognized as an important approach in cardiac rehabilitation [16]. Particularly, two meta-analyses have shown favorable effects of exercise on attenuation of N-terminal pro-brain natriuretic peptide (NT-proBNP) [17] and mitigation of LV remodeling [18] in patients with heart failure. Also, in the oncological setting, it has become clear that exercise is a safe and effective supportive therapy in the management of several treatment-related side effects and in improving overall physical fitness [19, 20]. Furthermore, in a recent position paper the European Society of Cardiology task force for cancer treatments and cardiovascular toxicity suggests the possible utility of aerobic exercise as a promising strategy to attenuate ARC [21]. However, this position remains to be complementarily analyzed as the evidence so far is mainly from studies in animal models [22, 23], with only a few studies in a limited number of patients to evaluate the cardioprotective role of exercise in cardiac function among women with breast cancer receiving cardiotoxic treatments [24–26]. Further clinical studies involving a large sample size and accurate clinical biomarkers are thus warranted to better understand the effectiveness of exercise in the mitigation of ARC.

### Hypothesis

The primary aim of this study is to ascertain whether a structured exercise program mitigates ARC, measured by change in the levels of circulating biomarkers (NT-proBNP) and cardiac (dys)function endpoints (LV global longitudinal strain and LVEF). The secondary aim is to evaluate the effectiveness of the intervention in the regulation of some cardiac health parameters: resting blood pressure, resting heart rate (HR), resting HR variability (HRV) and recovery HR. As exploratory objectives, we will assess physical function (cardiorespiratory capacity, upper limb strength, and lower limb functionality), self-reported physical activity level, health-related quality of life (HR-QOL), and fatigue. We hypothesize that exercise may limit the degradation of cardiac function and structure and benefit cardiac outcomes. We also believe that patients in the intervention group will improve overall physical fitness, HR-QOL, decrease their perception of fatigue, and increase physical activity levels.

## Methods/design

### Study design

This is a study protocol for a two-arm, prospective, randomized controlled trial that will explore the cardioprotective effect of a structured exercise program, compared to standard care, in adult women undergoing anthracycline-containing chemotherapy (AC-CT) for early BC. The study design and protocol adhere to the Standard Protocol Items: Recommendations for Interventional Trials (SPIRIT) guidelines (Additional file 1). The study design is outlined in Fig. 1.

**Fig. 1 Fig1:**
[figure not shown]
Study flow. ACH, anthracycline-containing chemotherapy; SBCC, standard breast cancer care; SEP, structured exercise program

### Ethical approval

This study will be conducted in compliance with the Declaration of Helsinki Ethical Principles (1975) and it received approval by the Ethics Committee of the Centro Hospitalar de Vila Nova de Gaia/Espinho (CHVNG/E; Vila Nova de Gaia, Portugal) (reference number: 145/2018–1). The study is registered in the International Standard Randomised Controlled Trial Number (ISRCTN32617901). Any protocol amendments will be submitted to the CHVNG/E for ethical approval and updated on the ISRCTN.

### Participant recruitment

We intend to recruit 90 adult women with early invasive BC, scheduled to receive AC-CT and followed up in the Medical Oncology Department of the CHVNG/E. Participants will be recruited based on the eligibility criteria presented in Table 1. Recruitment will take place in two distinct phases. In the first instance, potential participants will be identified in the multidisciplinary consultation involving medical oncologists, surgeons, and radio-oncologists. After this preliminary phase, the eligibility of each patient will be confirmed by the oncologist during a medical consultation. The oncologist will present the study to the patients who are considered eligible, explaining the study, offering participation and requesting written informed consent. Written informed consent will be obtained from all patients and they will be informed that they are under no obligation to participate and they may withdraw their consent at any time. Withdrawal from the study or non-participation will have no consequences for medical follow up and care. Where possible, the reasons for withdrawal from the study will be recorded. All the participants will be followed from the acceptance period (t0) and 3 months after the end of the AC-CT (t3). If recruitment is not achieving the target sample size, we will extend recruitment to additional hospitals.

**Table 1 Tab1:** Eligibility criteria

Inclusion criteria	Exclusion criteria
Female gender	Contraindications to maximal exercise testing Decompensated diabetes mellitus
Aged 18 years or older	Severe anemia (hemoglobin < 8 g/dL) uncorrectable with transfusion and/or iron and/or vitamin deficiency replacement Pregnancy
Histological diagnosis of stage IA–IIIC breast carcinoma	Known significant heart disease (myocardial infarction, congestive heart failure, cardiomyopathy)
Scheduled to receive AC-CT	Usual medication containing beta-blockers
Follow up at the Medical Oncology clinic at the CHVNG/E	
Consent of the assistant oncologist for the practice of exercise	
Able to provide informed consent	
Acceptance of randomization to intervention group or control group	

*AC-CT* anthracycline-containing chemotherapy, *CHVNG/E* Centro Hospitalar de Vila Nova de Gaia/Espinho

### Randomization

After confirmation of eligibility and baseline assessments (t0), patients will be randomized using Internet software (www.sealedenvelope.com), in a 1:1 ratio to the supervised exercise group (intervention group) or the usual care group (control group), using a permutated block design with random block sizes (4, 6, 8) with stratification by two dichotomous variables, which are known risk factors for ARC:Age (< 50 years or older)Receiving anti human epidermal growth factor receptor 2 (anti-HER2) therapy (yes/no)

This process will be performed by an external individual who is blinded to the study and who will place the sequence in a numbered, opaque, sealed envelope. The allocation of participants will then be reported to an oncologist (AJ) who will subsequently inform the patients about the assignment group.

### Study arms

#### Intervention group

Patients allocated to the intervention group will perform a supervised exercise program specifically developed for patients with BC, based on the guidelines of the American College of Sports Medicine [27] and in a close cooperation between physical sports researchers (PA, DE, AA) and medical staff (oncologists, surgeons, radiologists, physiatrist, and physiotherapist) of the CHVNG/E. The exercise program comprises three sessions per week guided in small groups (< 5 patients) in an appropriately equipped room at the CHVNG/E, supervised by the main author (PA) and a physiotherapist. Each session will involve an initial warm up (5 min), followed by resistance and aerobic training (60 min), and ending with a cooldown phase (5 min). The program will be started 1–2 days after the first AC-CT session and will be conducted over the respective treatment of each patient. It should be noted that the proposed exercise intervention will never be intended to replace or interfere with the current standard BC care.

##### Aerobic training

It will include the combination of treadmill, stationary bike, and stepping. This phase will be monitored through HR (each participant will wear a HR monitor during exercise training sessions) and rate of perceived exertion (RPE) measured by a 0–10 point modified Borg scale (minimal effort = 0; maximum effort = 10) [29]. During the first 2 weeks, the participants will perform 20 min (divided equally among the three exercise modes) of light-intensity, aerobic training (at < 50% of measured HR reserve (based on maximum HR reached in the cardiorespiratory test), with a reported rating of 2–4 (“easy” to “somewhat easy”) on the modified Borg scale). After this period, 3 min will be added every 2 weeks until a volume of 30 min of aerobic training is reached. At this stage, participants will be encouraged to perform moderate-intensity to high-intensity training (at 65–80% of measured HR reserve, with a reported rating of 5–8 (“somewhat hard” to “hard”) on the modified Borg scale) until the end of the intervention.

Participants will be reminded weekly (by email and phone) of their exercise training schedule and the importance of adherence, to achieve the established objectives.

##### Resistance training

Resistance training will include upper body (shoulder press, chest press, lateral pulldown, biceps curls, and triceps extension) and lower body (squat, calf raise, leg press, leg extension, and leg curl) weight-training exercises. All the exercises will be performed at the maximum possible joint range of motion, using resistance machines and free weights. RPE will be measured using a 0–10-point OMNI-Resistance Exercise Scale (OMNI-RES, minimal effort = 0; maximum effort = 10) [28]. During the first week, participants will perform 2 sets and 10 repetitions of each exercise without additional resistance or with the lowest available (reported rating of 2–4 (“easy” to “somewhat easy”) on the OMNI-RES). After this phase, if no adverse events or symptoms were reported for a specific exercise, resistance will be added so that each participant could be able to perform 3 sets with 12 maximal repetitions (12-RM) of each exercise. When the participants can complete 3 sets and more than 12-RM at the set weight in three consecutive sessions, then the resistance will be increased by between 5% and 10%.

### Usual care group

Patients allocated to the usual care group (CG) will receive standard BC care. The usual CG will not receive any specific advice about physical activity and will not be asked to be inactive. In compensation for participation in this study, patients in this group will be offered the possibility to follow the same exercise program as in the intervention group, after the final assessments are completed.

### Study assessments

The schedule of study outcome assessments is outlined in Fig. 2. Study assessments will be scheduled upfront and participants will be regularly reminded (by email and phone) to ensure complete follow up. Primary, secondary, and exploratory outcomes will be measured in all participants at three different time points:t_0_ (baseline assessments): between 0 and 14 days prior to the first chemotherapy sessiont_2_ (post-treatment assessments): between 1 and 5 days after the end of AC-CTt_3_ (follow-up assessments): after 3 months of t_2_

**Fig. 2 Fig2:**
[figure not shown]
The schedule of enrolment, interventions, and assessments. -t_0_, enrolment process; t_0_, baseline; t_1_, during anthracycline-containing chemotherapy; t_2_. post anthracycline-containing chemotherapy (which coincides with the end of the intervention); t_3_, 3 months after t_2_; NT-proBNP, N-Terminal pro-brain natriuretic peptide; LV, left ventricular

In addition, for analysis of circulating NT-proBNP, blood samples will be collected between 1 and 24 h before each AC-CT cycle (t_1_: during treatment assessments). Patients will be instructed and reminded to avoid drinking beverages containing alcoholic or caffeine, and to abstain from smoking for 12 h prior to, and avoid vigorous physical activities for 24 h prior to all examinations.

### Study outcomes

#### Primary outcomes

The primary outcomes are:Circulating NT-proBNP levelsResting LV global longitudinal strainResting LV ejection fraction

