### Sample size calculation

The sample size was determined by a power calculation based on resting LVEF outcome, using a non-commercial statistical power analysis program (G*Power Version 3.1.9.2). Based on an effect size of 0.6 for resting LVEF presented in a previous study [26], to ensure statistical power of 80% and a significance level of 0.05, using the *t* test for two independent groups, the recruitment of 72 participants is required. Predicting a 20% dropout rate [19], we estimate that a total of 90 patients will be needed (45 in each arm). There are no planned early stopping rules. Adverse events will be evaluated by the study investigators, who will make the decision to stop the study early if there is a clinically relevant increased risk.

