### Statistical analyses

Statistical data analysis will be performed using the Statistical Package for the Social Sciences. The statistical significance will be set at a *p* value <0.05. Intention-to-treat and per-protocol approaches will be used both for all analyses. Data analysis will start with standard descriptive methods to describe the data (means and standard deviations will be calculated for continuous variables and absolute and relative frequencies for categorical variables).

Continuous variables will be compared between the two study groups using one-way analysis of covariance (ANCOVA), adjusted for the effect of the baseline values (covariate). A linear two-way mixed ANCOVA model with repeated measures (t1, t2 and t3) will be performed to test the difference over time between the two study groups and interaction (Group × Time), on primary and secondary outcomes, with the same covariate as the one-way ANCOVA. Bonferroni’s post-hoc procedure will be performed to locate the pairwise differences. Normality will be verified by the Kolmogorov-Smirnov test and the homogeneity of the variance will be validated by Levene’s test. Effect size will be calculated to estimate variance between moments through partial eta-squared. The cutoff values were defined as 0.02 for small effect size, 0.13 for moderate, and 0.26 for large effect sizes [36]. The chi-squared test will be used to check for a relationship between categorical variables. The effect size will be calculated using Cramer’s V test and interpreted based on the following cutoff values: 0.10 for a small effect, 0.30 for a medium effect, and 0.50 for a large effect. [36] No interim analyses will be conducted.

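### Three unranked primary outcomes are each tested at an unsplit 0.05 in two analysis sets, and the only multiplicity step does not reach across outcomes or sets

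*Protocol article*

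**What the plan says.** All from the Protocol article.

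- **Outcomes.** Primary outcomes: "The primary outcomes are:Circulating NT-proBNP levelsResting LV global longitudinal strainResting LV ejection fraction". The Abstract and the Hypothesis section name the same three, and nowhere is one placed above the others.
- **Threshold.** Statistical analyses: "The statistical significance will be set at a *p* value <0.05". It is not divided between outcomes, and sidedness is not stated.
- **Analysis sets.** Same section: "Intention-to-treat and per-protocol approaches will be used both for all analyses". Neither set is named as leading.
- **Times.** Study assessments: "Primary, secondary, and exploratory outcomes will be measured in all participants at three different time points", namely baseline, t2 and t3. NT-proBNP has further samples during treatment (t1): "blood samples will be collected between 1 and 24 h before each AC-CT cycle". No visit is named as the deciding one.
- **Models.** "Continuous variables will be compared between the two study groups using one-way analysis of covariance (ANCOVA), adjusted for the effect of the baseline values", with no visit given, and also "A linear two-way mixed ANCOVA model with repeated measures (t1, t2 and t3) will be performed to test the difference over time", which yields group and Group × Time tests.
- **Multiplicity.** The only adjustment stated is Bonferroni for post-hoc pairwise differences.
- **Sample size.** "The sample size was determined by a power calculation based on resting LVEF outcome". The article does not go on to make LVEF the outcome that decides the trial.

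**The concern.** The primary aim is to find out whether exercise mitigates anthracycline-related cardiotoxicity. As written, that claim could rest on NT-proBNP, strain or LVEF, at t2 or t3, in ITT or per-protocol, each judged against 0.05. Bonferroni after the repeated-measures model works within one outcome and one analysis set, so it does nothing about the three-way choice of outcome or the two-way choice of set.

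Two things are at stake. The 5% error rate need not hold for the headline claim. And if the results disagree (LVEF null and NT-proBNP positive, or ITT null and per-protocol positive), the text gives no way to say what the trial concluded, so the choice could be made after the data are seen.

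**Working it through.** **Inputs from the article.** Three primary outcomes, 0.05 per test, two post-baseline visits common to all outcomes (t2, t3), two analysis sets, no interim analyses. Sample size: standardised effect 0.6, 80% power, 0.05, two-group t test, 72 evaluable, 20% dropout, 90 recruited.

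**Assumptions, not in the article.** Any one significant result counts as success. Correlation between outcomes 0 to 0.7, between t2 and t3 0.5 to 0.7, between ITT and per-protocol 0.9. Correlated cases come from multivariate-normal simulation (400,000 to 1,000,000 draws) with two-sided tests.

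**Step 1: the plan's own figure.** A noncentral-t calculation with 36 per arm (72 in all), effect 0.6 and one-sided 0.05 gives 80.9% power, and 72/(1 − 0.20) = 90. The stated numbers reproduce. With a two-sided test the same 72 give 71% power. Sidedness is a separate point; it matters here only because the cost of any adjustment has to be shown both ways.

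**Step 2: three outcomes, one visit, one set.**
- Independent: 1 − 0.95³ = 14.3%.
- Outcome correlation 0.3, 0.5, 0.7: 13.6%, 12.6%, 10.9%.

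**Step 3: three outcomes at two visits.**
- All six independent, unadjusted: 1 − 0.95⁶ = 26.5%.
- Unadjusted, visit correlation 0.5 to 0.7: 24.9% to 22.9% at outcome correlation 0; 23.7% to 21.9% at 0.3; 22.0% to 20.3% at 0.5; 19.2% to 17.6% at 0.7. That is about 18–25%.
- If Bonferroni covers the two visits (0.025 each, visit correlation 0.5): 13.3%, 12.8%, 11.9% and 10.5% at outcome correlation 0, 0.3, 0.5 and 0.7. That is about 10–13%.

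**Step 4: adding per-protocol.**
- Three outcomes, one visit, both sets: 19.7% (outcome correlation 0) down to 15.0% (0.7).
- All 12 tests, unadjusted, visit correlation 0.5 to 0.7: about 24–33%.

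The t1 samples of NT-proBNP and the separate group and Group × Time tests are not counted.

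**Step 5: direction.** These rates include false findings of harm. Counting only false claims of benefit from two-sided tests, independence gives 1 − 0.975³ = 7.3% for three tests and 1 − 0.975⁶ = 14.1% for six, against 2.5% for a single test.

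**Step 6: after adjustment.** Testing each outcome at 0.05/3 = 0.0167 at one visit in one set, which is the first step of Holm, gives a family-wise error of 1 − (1 − 0.05/3)³ = 4.9% if independent and 4.8% to 3.9% for correlation 0.3 to 0.7. Power for LVEF at that step (36 per arm, effect 0.6) is 54% two-sided or 65% one-sided. Holding 80% at that step would need 120 evaluable (150 recruited) two-sided or 102 (128) one-sided.

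**The case against.** **The text never says that one significant outcome is enough.** This stands as a condition on every rate above. If all three outcomes had to be significant, the error would be at most 5% and the cost would fall on power. How large that cost is cannot be worked out from the article: it gives no effect size for strain or NT-proBNP and no correlations.

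**A reader might infer a flat error rate of 14–25% in place of 5%.** The documents do not support that. The 14.3% is the value under independence, not a floor. The article describes LVEF and strain together as apical-view echocardiographic measures, so some correlation is likely, and 11–14% is the fairer range for the outcomes alone. The 25% end needs separate unadjusted tests at t2 and t3. The planned Bonferroni step may well be meant for exactly those comparisons, and then the figure is about 10–13%. Nor does 14–25% include the per-protocol analyses.

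**A reader might infer that ITT and per-protocol are declared equal.** The article says only that both are used throughout; it ranks neither.

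**An unseen statistical analysis plan may hold a decision rule.** It may. But the article positively states three unranked primaries, one undivided threshold and both sets for every analysis. A rule that narrowed these would change what is published, and which result decides the trial belongs in the protocol.

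**LVEF is a debatable gatekeeper.** This stands. The Background says that biomarker elevation and strain impairment come before LVEF decline, and the Discussion reports that the non-randomised study behind the assumed effect size saw no relevant echocardiographic change. It bears on which remedy to choose, not on whether one is needed.

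**Conclusion.** The concern holds in a conditional form. Following the article as written, the main conclusion can rest on any of several tests at 0.05, and the one stated adjustment does not reach across outcomes or analysis sets.

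If any one significant result counts as success, the family-wise error is:
- about 11–14% for three outcomes at one visit;
- about 10–13% for two visits if Bonferroni covers them;
- about 18–25% for two visits if it does not, with 26.5% as the fully independent case;
- higher again once per-protocol results are eligible.

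All these rates rest on assumed correlations and count errors in either direction. Even on the reading kindest to the plan, where Bonferroni handles the visits, the error is at least about twice the nominal 5% over the correlations considered.

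**What to change.** Before any unblinded analysis, state in the protocol, any analysis plan and the registry entry:

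1. ITT is the deciding analysis set.
2. One post-baseline visit is the deciding time. The natural choice is t2, which the Fig. 2 legend equates with the end of the intervention.
3. One of two rules for the three outcomes at that visit:
   - **Holm at an overall 0.05:** the smallest p-value is compared with 0.0167, the next with 0.025 and the last with 0.05, stopping at the first failure; or
   - **fixed sequence:** LVEF, on which the sample size rests, as the single primary at 0.05, followed by strain and NT-proBNP in a pre-specified order, each tested only if the one before it succeeds.
4. Results at t3 and in the per-protocol set are supportive.

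**Cost.** One paragraph, with the ethics submission and registry update that the article already requires for amendments. Holm keeps all three outcomes in play but lowers first-step power for LVEF to about 54% two-sided or 65% one-sided at 72 evaluable, unless the sample grows as shown in the working. The fixed sequence costs LVEF no power and needs no extra patients, but strain and NT-proBNP become descriptive if LVEF fails. That is a real risk, since the article itself says they change earlier. The choice of rule, and the order within a sequence, is therefore for the investigators.
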